### Data collection

#### Data collection tool and variables

During the second phase of the study, data will be collected through questionnaires and analytical procedures. This integrated approach will yield a comprehensive dataset, enhancing the study’s clinical and environmental assessment as a whole.

*1*. *Questionnaires*. The questionnaires have undergone a meticulous design process, incorporating both newly formulated sections and standardized or adapted questions from previously employed surveys in published studies [24–28]. To ensure their effectiveness, these questionnaires have been subjected to multiple revisions by experts across various departments within the field. This comprehensive review aimed to guarantee that the questions align with the constructs intended for assessment. Upon the initial phase of data collection, the robustness of these questionnaires will be further evaluated. Internal consistency will be assessed using the Cronbach’s alpha test, ensuring that the questions within each questionnaire measure the intended constructs reliably. This rigorous evaluation process is integral to maintaining the quality and precision of the data we aim to collect.

The following information will be collected through the questionnaires:

Environmental characteristics of the settings (including surfaces, volumes, ventilation, and common areas), daily activities performed, and hygiene practices within the facilitiesIndividual participant characteristics including general attributes, existing medical conditions such as respiratory infections and allergies, vaccination history, exposure to risk factors, socio-economic factors, any acute illnesses experienced during the study period, contact history with other individuals, and their consent for potential nasopharyngeal swab testing.

*1*.*1 Environmental questionnaire*: The purpose of this questionnaire is to understand the current hygiene policies and practices within the facilities and to identify factors that might influence the risk of ARIs.

The environmental questionnaire (EQ) is specifically designed for the managers of the various settings. It evaluates the environmental structure and conditions, as well as individual and group behaviour and practices within these settings.

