The questionnaire will cover several aspects, including personal and environmental hygiene practices, cleaning and disinfection of common areas, ventilation, air quality and daily activities. It will consist of a series of multiple-choice and open-ended questions to cover different environmental factors in order to obtain specific information on participants behaviour, their movements and contacts within the facility. In addition, the questionnaire will assess the efficacy of existing policies on preventing the spread of respiratory viruses, as well as the facility’s ability to adopt any policy changes in a timely and effective manner. The EQ will be administered once at the beginning of the survey to the facility managers and will be administered again later if there are substantial changes in the facility. The questionnaire will take approximately 8 minutes to complete.

*1*.*2 Baseline clinical questionnaire*: The objective of the baseline clinical assessment questionnaire (BCQ) is to provide a complete and accurate picture of the participant’s clinical status, identifying potential risk factors and individuals susceptible to developing complications from ARIs. The questions have been crafted by combining established question formats, including inquiries about pre-existing respiratory symptoms, allergic history, and risk factors [24–26], with the integration of newly devised questions designed to align with the objectives of our project.

The BCQ is intended for all participants and consists of a series of multiple-choice and open-ended questions covering different aspects of the participant’s medical history, such as the presence of previous illnesses, risk factors for respiratory infections, previous vaccinations, respiratory and allergic symptoms, socio-economic factors, and exposure to risk factors such as smoking and alcohol consumption. The data collected by the BCQ will allow a baseline assessment of the subject’s condition and evaluate a possible correlation with respiratory virus infections. The BCQ will only be administered once at the beginning of the survey, or when a new participant joins the study (e.g. transfer to the facility). The questionnaire will take approximately 12 minutes to complete.

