*1*.*3 Acute clinical assessment questionnaire*: The objective of the Acute Clinical Assessment Questionnaire (ACAQ) is to collect information that will allow us to monitor the evolution of the subject’s condition over time, to identify possible clusters of respiratory infections within the community environment, and to take the necessary prevention and control measures to prevent the spread of infection. The questions have been formulated by merging established question formats pertaining to acute symptoms and manifestations [27, 28] with newly integrated inquiries that specifically align with the objectives of our project.

The ACAQ is an essential tool for the early identification of any symptoms associated with ARIs and for monitoring the evolution of the subject’s condition over time. It is designed to identify all participants presenting with respiratory symptoms, such as cough, sore throat, difficulty breathing or fever, and is intended to provide a detailed and timely clinical assessment of participants. The questionnaire consists of a series of specific questions regarding the subject’s current symptoms, the duration of symptoms, any current therapies and contact with other individuals who have experienced similar symptoms. The completion of each questionnaire will take approximately 6 minutes.

*1*.*4 Methods of questionnaire administration*: The questionnaires will be administered with different methods and supports based on the target. The method of administration, support and frequency are summarised in **Table 1** for each setting and target population.

**Table 1 pone.0309111.t001:** Types and methods used for the questionnaires in the various settings of the Stell-ARI study.

Type of questionnaires	Setting	Target	Method of administration	Support	Frequency
Environmental Assessment Questionnaires	LTCF	Head of facility manager	Self-administered	Paper form	1 time and in case of changes
	Prison				
	School				
Baseline clinical evaluation questionnaires	LTCFs	Residents	Interviewer-administered	Tablet	1 time at the beginning and for new entries
		Staff	Self-administered		
	Prison	Inmates	Interviewer-administered	Paper form	
		Staff	Self-administered		
	School	Parents of students and Staff	Self-administered	’Influweb’ platform	
Acute Clinical Assessment Questionnaires	LTCF	Residents	Interviewer-administered	Tablet	In case of new occurrence of Symptoms
		Staff	Self-administered		
	Prison	Inmates	Interview	Paper form	
		Staff	Self-administered		

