### Outcomes of the study

The impact of ARIs is greatest in fragile and disadvantaged populations [43]. Our project has a clear public health focus: to reduce incidence of ARIs, limit their economic burden on the NHS, and address inequalities in disease burden related to age and marginalisation. While the protocol is developed and piloted within selected facilities in Tuscany Region, the methodology applied, and the findings can be generalised at national/international levels in similar settings. The expected outcomes corresponding to each specific objective are detailed below.

Sentinel clinical surveillance system for acute respiratory diseases will be established, with data collection tools (questionnaires) for clinical surveillance and risk factors tested and validated in different indoor settings such as LTCFs, prisons, and schools.Indoor air quality assessment instruments and tools will be validated in the above-mentioned settings. Additionally, methods and strategies for assessing air and surfaces microbial contamination will be validated in the same settings. Methods and strategies for WBE will also be validated for the same selected communities.An integrated environmental and clinical surveillance system will be established and tested for closed settings. This will involve:
Assessing the connection between respiratory disease incidence, environmental and individual risk factors, and wastewater viral load. A predictive model using a nomogram will be developed, validated, and applied;Validating a QMRA model for different viruses and settings;Providing recommendations for expanding the integrated surveillance system of ARIs for early warning and pandemic preparedness efforts.

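### Cronbach's alpha applied to each questionnaire cannot show that multi-domain factual inventories measure anything reliably, and with about three respondents it is not usefully estimable for the environmental questionnaire

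*Protocol article*

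**What the plan says.** The Questionnaires paragraph under Data collection tool and variables names one reliability statistic, Cronbach's alpha as a measure of internal consistency, and says what it will achieve: "ensuring that the questions within each questionnaire measure the intended constructs reliably". The same paragraph reports that new items were combined with standardised or adapted ones from published surveys, and that "these questionnaires have been subjected to multiple revisions by experts across various departments within the field".

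The three instruments are then described.

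- **EQ** (section 1.1): premises, ventilation, cleaning, daily activities and policies. "It will consist of a series of multiple-choice and open-ended questions to cover different environmental factors". On who answers: "The EQ will be administered once at the beginning of the survey to the facility managers". It is repeated only if a facility changes substantially. Table 1 gives the target as the head of each facility, and there are three facilities.
- **BCQ** (section 1.2): it "consists of a series of multiple-choice and open-ended questions covering different aspects of the participant’s medical history", together with vaccination, respiratory and allergic symptoms, socio-economic factors, smoking and alcohol. It is given once per participant.
- **ACAQ** (section 1.3): "a series of specific questions regarding the subject’s current symptoms, the duration of symptoms, any current therapies and contact with other individuals". The response format is not stated.

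No summed score or scale is described for any of them. Under Outcomes of the study, the first expected outcome includes "data collection tools (questionnaires) for clinical surveillance and risk factors tested and validated in different indoor settings".

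**The concern.** This is more than a detail left to a fuller document. The article fixes the statistic, ties it to each questionnaire and states the inference to be drawn, and that inference does not follow. Alpha is a function of the item variances and the variance of their sum. It speaks to reliability only when the items are scored numerically and meant to add up to one quantity. Vaccination status and alcohol use need not correlate for both to be reported correctly, and free text has no score unless it is coded.

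At stake is the questionnaire part of the validation outcome. An alpha value could be published as evidence of reliability when it carries little information on that. Answers to the BCQ also serve as exposures in the logistic models, and questionnaire-based exposure frequency and duration feed the QMRA dose. Repeatability of those answers therefore matters, and a whole-questionnaire alpha would not reveal it. No power or error rate of the study changes.

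**Working it through.** The plan gives no target, expected value or sample size for alpha, so there is no figure of its own to reproduce. The checks below ask what alpha would show for instruments of the kind described. Item counts (k) and mean inter-item correlations (r) are assumptions, because the article gives neither.

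**1. Accurate but unrelated facts.** Formula: alpha = k/(k-1) × (1 - sum of item variances / variance of the total). Independent yes/no items were simulated without any response error for 380 people, the number in the Sample size section.

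- k = 10: mean alpha about -0.01, 95% range -0.17 to 0.13.
- k = 20: mean alpha about -0.01, 95% range -0.17 to 0.13.

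Perfectly answered items can thus give an alpha near zero.

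**2. Dependence on length.** Formula: standardised alpha = k·r / (1 + (k-1)·r). With r = 0.05:

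- k = 10: 0.50/1.45 = 0.34
- k = 20: 1.00/1.95 = 0.51
- k = 40: 2.00/2.95 = 0.68

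With k = 20, alpha is 0.29, 0.51, 0.69 and 0.83 for r = 0.02, 0.05, 0.10 and 0.20. At a fixed weak correlation the value doubles between 10 and 40 items, with no change in the quality of any single answer.

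**3. The EQ.** There are three facilities with one head each, so n is about 3. Repeats after a change in a facility add no independent respondents. Feldt's interval uses (1 - alpha)/(1 - observed alpha) ~ F with n-1 and (n-1)(k-1) degrees of freedom. With n = 3, k = 20 and an observed alpha of 0.70:

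- Degrees of freedom: 2 and 2 × 19 = 38.
- F quantiles: 4.07 (97.5%) and 0.025 (2.5%).
- Lower limit: 1 - 0.30 × 4.07 = -0.22.
- Upper limit: 1 - 0.30 × 0.025 = 0.99.

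The assumed k matters little. With k = 10 the upper quantile is 4.56 and the lower limit is 1 - 0.30 × 4.56 = -0.37. With k = 40 it is 3.87, giving 1 - 0.30 × 3.87 = -0.16. The upper limit stays at 0.99.

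Simulation with n = 3 and k = 10 agrees. When the true alpha is 0.8, sample values run (95% range) from about -7.8 to 0.96. When it is 0, they run from about -35 to 0.76. Three respondents can hardly tell these two cases apart.

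**4. What other evidence the article states.** Expert revision and borrowed questions bear on content. The article states no test-retest, inter-rater or mode-of-administration comparison. The BCQ is given once per person, so no retest data arise. Table 1 mixes interviewer administration and self-completion, on tablet, paper and web.

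**The case against.** Several replies have force.

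- **Alpha may be meant per construct.** The sentence speaks of constructs in the plural, and which blocks are scored could sit in a fuller document. This is possible, but the section describes no scored block, and most of the listed content (ventilation, vaccination, therapies, contacts) would not form one. Some symptom items may correlate, so alpha for a respiratory or allergic symptom block would be legitimate if it is scored.
- **Alpha is not the only quality step.** Expert review and adapted published items count towards content validity, and the article does not say that alpha is the sole basis of validation. Both points stand. They leave alpha as the only stated reliability check.
- **The EQ may lie outside the first outcome**, which concerns clinical surveillance and risk factors; environmental tools come under the second. The text does not settle this. The commitment to compute alpha covers the EQ either way.

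A reader might also infer more than the documents support. One inference is that the check would reject good questionnaires or pass poor ones, but no threshold or accept/reject rule is given. Another is that a long questionnaire yields a high alpha whatever its accuracy. At r = 0.05 the values above reach only 0.68 at 40 items, and random response error lowers alpha. A third is that all three instruments are open-ended, which is stated for the EQ and BCQ only.

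**Conclusion.** The point holds in a limited form. The sentence attributes to alpha a property that it cannot deliver for these instruments as described. For the EQ, alpha is not usefully estimable: about -0.22 to 0.99 around an observed 0.70, assuming 20 items and three respondents, and much the same for 10 or 40 items. For the BCQ and ACAQ, a whole-questionnaire alpha reflects item overlap and length and does not establish that answers are accurate or repeatable. The size of that effect depends on assumed item counts and correlations.

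The consequence is confined to the questionnaire validation claim, to which alpha adds little beyond the content support already described. Alpha does not enter the regression, time series or QMRA models, and it would be wrong to conclude that those analyses are invalid on this account. The correction is worth making because it is cheap and the claim is a named outcome.

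**What to change.** 1. Drop alpha for the EQ and for factual or open-ended items.
2. Report alpha per block, and only where items are scored as one multi-item scale, for example a respiratory or allergic symptom block if it is scored. Name those blocks in advance.
3. Describe the EQ and the factual items as expert-reviewed, not as shown to be reliable, and word the first expected outcome to match.
4. Report item completion for each questionnaire.
5. For the ACAQ, describe how symptom combinations agree with the swab PCR already planned. State that this covers only swabbed symptomatic cases and the target viruses, so an infection with another respiratory virus would appear as a disagreement.

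A cross-check against facility health records should not be relied on: the article does not list them as a data source, and linking to them would be new data processing.

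The cost is changed wording and a few descriptive tables from data already being collected. The downside is a more modest validation claim.

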Wastewater Based Epidemiology (WBE), initially introduced for the poliovirus surveillance, has shown its high potential, especially during the COVID-19 pandemic, making it a very promising tool for monitoring various infections as well as for antimicrobial resistance [9, 10]. In the COVID-19 pandemic scenario, it has been a valuable instrument for understanding the full extent of viral circulation and as an alert system during a rise of SARS-CoV-2 infection [7, 11]. Most people infected with SARS-CoV-2 are asymptomatic, but they shed viral particles, particularly in faeces and other body fluids, which ultimately reach sewage systems. Therefore, detecting the genome of SARS-CoV-2 in urban wastewater has been useful in capturing the full extent of the disease at a community level, although the viral genome in this matrix is not associated with infectivity [12].

WBE can detect pathogen circulation before the onset of cases, making it a valuable early warning tool and facilitating the timely identification of new variants. This approach has been extensively used, not only in large urban areas but also in smaller communities, to identify the initial introduction of pathogens, even in the absence of symptomatic infections, enabling the implementation of prevention and control measures [13].

Both types of surveillance have strengths and limitations and may be susceptible to bias. A surveillance system integrating data from multiple sources may overcome these challenges and better describe the epidemiological scenario of ARIs. This integration is particularly useful in enclosed settings, especially for individuals who may experience vulnerabilities, increasing their risk of developing ARIs and/or experience more serious clinical consequences, such as age (children or the elderly), underlying health conditions, or socio-economic disadvantage.

While WBE studies have been carried out in LTCFs [14] and schools [15] to implement prevention measures, an integrated surveillance approach is lacking. Data are even more limited for prisons [16], which pose a high risk for ARIs due to the prevalence of additional risk factors (e.g. substance use, including tobacco, suboptimal individual hygiene) and environmental factors such as overcrowding and infrastructural deficiencies (e.g. ventilation systems).

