Bacterial counts will be obtained by using an impactor sampler, with Rodac plates containing Plate Count Agar (PCA) or selective medium. Subsequently, the plates will be incubated.Viral analysis will be performed by using Impinger Sampler, consisting of an air inlet structure and a collection vessel filled with a liquid medium, Viral Transport Medium (VTM) [32].

Surface sampling will also be conducted in these areas on a monthly basis. Sterilized swabs will be swiped across 36 cm^2^ areas [33]. For viral analysis, virus will be eluted from the swabs with 1 mL of 3% beef extract solution at pH 9, whereas for bacteriological analysis elution will be performed with 0.9% NaCl solution [34].

In wastewater analysis, the primary focus will be on target viruses. Trained personnel will perform weekly sampling at the exit point of each facility via a sewer drain outside the building. Necessary safety measures, including the use of PPE, will be strictly applied. A passive sampling method will be employed, as suggested for small communities with irregular sewage flow [35]: this involves immersing passive materials (electronegative filter membranes or gauze swabs) into the wastewater flow and leaving them for an extended duration [36]. Viruses will subsequently be eluted from these passive materials with 1 aliquot of sterile phosphate buffer solution. The solution will be centrifuged at 4500 rcf for 10 minutes to remove debris and then analysed using a commercial kit.

*2*.*3 Microbiological analyses*: Air and surface samples will be analysed for indicators of general/human microbial contamination (total bacterial load at both 22°C and 37°C, as well as Staphylococcus aureus and Escherichia coli) using conventional cultural methods. Specific respiratory viruses: Human Adenovirus (HAdV), Influenza Virus A and B (IVA and IVB), SARS-CoV-2, Respiratory Syncytial Virus Type A and Type B (RSVA and RSVB) will be detected using PCR techniques. The same RT-PCR protocols, summarised in **Table 2**, will be applied to both clinical and environmental samples. For wastewater samples, the amount of genome copies obtained will be adjusted on the basis of the sewage flow to estimate the daily viral emissions from the community.

**Table 2 pone.0309111.t002:** PCR protocols used for the detection of viral targets.

Virus	Target region	Primers and probes	Sequences (5′-3′)	Reference
SARS-CoV-2	ORF1ab region: nsp14	2297 CoV-2-F	ACA TGG CTT TGA GTT GAC ATC T	Verani et al., 2022 [37]

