### Statistical analysis and quantitative microbial risk assessment (QMRA)

#### Statistical analysis

Subject characteristics will be described by means of medians and interquartile ranges for numerical variables and absolute frequencies and percentages for categorical variables. The time course of the environmental variables will be presented through graphical displays.

Associations between infections detected via ACAQ and confirmed by clinical swabs (when necessary) and exposure factors detected by the QCB and the environmental air and surface monitoring will be assessed employing logistic regression models taking potential confounders into account. Statistical methods and analysis algorithms will be used to examine the collected data by proximity sensors and identify contact patterns, interaction frequencies and other relevant metrics.

WBE data will be normalised and adjusted to reduce variations arising from excretion and sewage flow. Environmental data will be treated as continuous variables, with regression models featuring splines used to estimate the time course of the measured parameters. The relationship between ARIs incidence and environmental data will be explored via time series regression models. In the event of missing data, imputation models will be employed, and sensitivity analysis will evaluate the impact of outliers on results. All analyses will encompass the entire dataset or stratified by setting. All statistical tests will be two-tailed with a significance level set at α = 0.05. Data analysis will be carried out using the R statistical software [41].

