#### QMRA

QMRA is a formal risk assessment process (based on a modified chemical risk approach) that includes the classical steps of hazards identification and characterization, exposure assessment, and risk characterization. This process involves formulating and applying models using fields and literature data to represent a scenario while addressing uncertainties. QMRA models will be designed and applied to the four selected target viruses and for the different settings in order to assess the risk of ARI based on environmental contamination measured by the microbiological air and surface monitoring. The contamination values, along with the estimated frequency and duration of exposure through inhalation and contact obtained from questionnaires, will be used to calculate the dose, which is the amount of pathogen assumed in a unit of time. Probabilities of infection and disease will then be estimated by applying virus-specific dose-response relationships. These probabilities will be expressed as functions that take into account variability and uncertainties, using Monte Carlo Analysis applied through Vensim software. A sensitivity analysis will also be performed to identify the most influential variables [42].

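### Flow-adjusted genome copies from passive wastewater samplers cannot be read as daily viral emissions; they support only a relative index within each setting

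*Protocol article*

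**What the plan says.** Section 2.2 (Environmental microbiological sampling) of the protocol article gives the method and the reason for it: "A passive sampling method will be employed, as suggested for small communities with irregular sewage flow". It describes the procedure as "immersing passive materials (electronegative filter membranes or gauze swabs) into the wastewater flow and leaving them for an extended duration", so two kinds of material are allowed and no deployment time is fixed. It continues: "Viruses will subsequently be eluted from these passive materials with 1 aliquot of sterile phosphate buffer solution".

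Section 2.3 (Microbiological analyses) then says, for wastewater, that the "genome copies obtained will be adjusted on the basis of the sewage flow to estimate the daily viral emissions from the community". The Statistical analysis section returns to the adjustment with a more modest purpose: "WBE data will be normalised and adjusted to reduce variations arising from excretion and sewage flow". It also allows analyses on the whole dataset as well as stratified by setting. The Outcomes section makes wastewater viral load one of the quantities to be related to the incidence of respiratory disease.

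**The concern.** Section 2.3 names a quantity (viral copies emitted per day by the community) and a route to it (adjustment for sewage flow). That route works for a sample of known volume: concentration times flow is a load. The sample described in section 2.2 has no known volume. What is eluted is the amount that stuck to the material while it hung in the sewer, so the PCR result is copies per sampler. Adjusting that for flow leaves an unknown multiplier in the answer.

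Two uses are at stake. First, any reported figure in copies per day would carry a unit that the data do not support. Second, if the three facilities are analysed together, differences in the multiplier would look like differences in shedding.

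**Working it through.** The article states no figure for daily emissions, so there is none to reproduce. The check is one of units.

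**Inputs from the article.** Passive sampler, membrane or gauze; deployment time not stated; one aliquot of eluate (all section 2.2). Adjustment by sewage flow to reach a daily emission (section 2.3). No uptake rate or calibration is given.

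**Notation.** C = viral concentration in sewage (copies/L); Q = flow (L/day); E = true daily load (copies/day); Rs = effective volume cleared by the sampler per day (L/day); t = deployment time (days); M = copies recovered per sampler.

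**Formulas**, assuming linear uptake:
- True load: E = C × Q
- Sampler catch: M = C × Rs × t
- Hence M × Q = E × (Rs × t), and E = M × Q / (Rs × t)

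Flow alone recovers E only if Rs × t happens to equal 1 L.

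**Illustration.** All values are assumed and none comes from the article. Take E = 1,000,000,000 copies/day and Q = 10,000 L/day, so C = 100,000 copies/L.

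| Rs (L/day) | t (days) | M (copies) | M × Q ÷ E |
|---|---|---|---|
| 0.1 | 0.25 | 2,500 | 0.025 |
| 0.1 | 7 | 70,000 | 0.7 |
| 1 | 1 | 100,000 | 1.0 |
| 1 | 3 | 300,000 | 3.0 |
| 1 | 7 | 700,000 | 7.0 |
| 10 | 0.25 | 250,000 | 2.5 |
| 10 | 7 | 7,000,000 | 70 |

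Over this range the computed emission runs from 0.025 to 70 times the truth, a span of 70 / 0.025 = 2,800-fold.

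**Within one setting.** On the log scale, log(M × Q) = log E + log(Rs × t). If material and deployment time are held constant, the last term is a constant and drops out of trends and of regression slopes.

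**Across settings.** The last term does not drop out. Two facilities with the same E and the same Rs = 1 L/day, one sampled for 1 day and the other for 3, would show a three-fold difference in computed emission with no difference in shedding.

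**Role of flow.** Without adjustment, M = E × Rs × t / Q, so a doubling of flow halves the catch at constant shedding. Adjustment with a measured Q removes that dilution. The adjustment is useful; it is the absolute unit that it cannot supply.

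**The case against.** The strongest reply is that the wastewater series is meant for early warning and time-series regression, where an unknown but stable constant does no harm, and that the Statistical analysis section claims only to reduce variation. That stands, and it limits the point to the absolute quantity. A reader might go further and infer that flow adjustment adds noise, or that the early-warning series is invalid. The algebra does not support either: with stable uptake, adjustment by measured flow removes a distortion, and an index without it would be more exposed to changes in flow.

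A second reply is that uptake rates, deployment times and flow measurement are details that an article leaves to its full protocol or to the cited methods. That is fair for the details, and their absence is not the finding. The finding is that section 2.3 affirmatively names a daily load as the result of adjusting a passive-sampler count for flow. The wording need not mean bare multiplication, but no other ingredient is mentioned.

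A reader might also infer that the QMRA is wrong in scale because PCR copies would be counted as infectious virus. The article does not say so. The QMRA is to "assess the risk of ARI based on environmental contamination measured by the microbiological air and surface monitoring", not by wastewater, and active air samplers and swabs of 36 cm² allow a concentration to be computed. The contamination values "will be used to calculate the dose, which is the amount of pathogen assumed in a unit of time", but the section also provides for literature data, virus-specific dose-response relations, Monte Carlo analysis and a sensitivity analysis. A genome-to-infectious ratio, or a dose-response curve in genome copies, fits within that. The Introduction's remark, "although the viral genome in this matrix is not associated with infectivity", concerns SARS-CoV-2 in urban wastewater, a different matrix. Any fold-overstatement of infection probability would have to assume a conversion error that the plan does not commit.

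**Conclusion.** The point holds for wastewater. The daily viral emission in section 2.3 is not identified from the sampling in section 2.2: it is off by the unknown factor uptake rate × deployment time, which may differ between membrane and gauze and between facilities. The size of the error cannot be taken from the article; the range of 0.025 to 70 rests on assumed uptake rates, assumed deployment times and linear uptake. The signal remains usable as a relative trend within a setting, provided that material and deployment time are held constant or accounted for. Comparisons of absolute level between facilities, and pooled models that ignore setting, are not supported.

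For the QMRA, no error in scale is shown. One clarification is worth asking for: the list of analytical procedures promises only the presence of pathogens in air and on surfaces, whereas the QMRA section needs quantities.

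**What to change.** **Wastewater.**
- Replace the daily-emission claim with a relative index: log copies per sampler, using one sampler material.
- Fix the deployment time, or record it and enter it in the model: log time as an offset if uptake is taken as linear, otherwise as a covariate.
- Keep the flow adjustment where flow is actually measured. Elsewhere use occupancy or another normaliser, and say which.
- Model the index within setting. In any pooled analysis use setting-specific intercepts or standardise within setting, and do not compare absolute levels across facilities.

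**QMRA (clarification only).** State that air and surface PCR results are quantified, and give the dose unit or the genome-to-infectious conversion used.

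**Cost.** No additional samples. Most of the change is wording and model specification. Standardising the material and fixing or recording deployment time is a field-procedure change, and the Study status section says that data collection is already under way; for samples already taken, material and times would have to come from field records. The price is that wastewater results are relative, not absolute.
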